**Study protocol**

**Seoul National University Hospital**

**Department of Radiology**

**Primary Investigator: [name] [name], PhD**

**Table of Contents**

1. Abstract ------------------------------------------------------------------------------------------------ 3

2. Background ------------------------------------------------------------------------------------------- 3

3. Objectives --------------------------------------------------------------------------------------------- 4

4. Endpoints ---------------------------------------------------------------------------------------------- 4

5. Eligible criteria ---------------------------------------------------------------------------------------- 5

6. Study design ------------------------------------------------------------------------------------------- 6

7. Required sample size -------------------------------------------------------------------------------- 6

8. Withdrawal criteria ---------------------------------------------------------------------------------- 6

9. General treatment guidelines ----------------------------------------------------------------------- 7

10. Follow-up -------------------------------------------------------------------------------------------- 9

11. Estimates --------------------------------------------------------------------------------------------- 9

12. Post-hoc subgroup analyses ---------------------------------------------------------------------- 10

13. Statistical analyses --------------------------------------------------------------------------------- 11

14. Ethical consideration ------------------------------------------------------------------------------ 12

15. References ------------------------------------------------------------------------------------------ 13

1. **Abstract**

This is a prospective, single-center, single-arm clinical study. The purpose of this study is to evaluate technical feasibility, safety, and clinical outcome of a novel separable cluster electrode for radiofrequency ablation (RFA) of hepatocellular carcinoma (HCC), in patients with focal liver malignancies

1. **Background**

According to the Barcelona Clinic Liver Cancer system, RFA is the only curative method among all non-surgical, locoregional treatment options in patients with HCC. RFA is also widely used as a curative treatment option for a variety of liver metastases, particularly colorectal liver metastases. Compared to surgery, RFA is less invasive, has less morbidity and requires shorter periods of hospitalization, yet provides comparable outcomes. Furthermore, the procedure is currently evolving as a competitor to surgery, especially in patients with single, small HCCs (< 3 cm in diameter). However, RFA is generally limited in creating a sufficiently large ablation volume for treating tumors larger than 2 cm in diameter with a sufficient tumor-free margin. Currently, various strategies are employed to create a sufficient ablation zone, including multi-tined or expandable electrodes to increase the surface area, internally cooled electrodes to diminish charring, perfusion electrodes to promote ionic availability, switching monopolar or multipolar controllers to provide a synergy of multiple applicators, and high-power generators to increase the power in order to overcome impedance. In this context, Lee et al recently reported that switching monopolar RFA using separable cluster electrodes (Octopus®, STARmed, Goyang, Korea), of which the inter-tine distances can be manipulated by the operator, was more efficient in creating a large ablation zone than using conventional cluster electrodes in an in vivo porcine study. This novel device may be more advantageous than conventional cluster electrodes by providing high flexibility to operators depending on the tumor size and shape, and by providing three times the active applicators with the same generator (i.e. a maximum of nine active tips are available with a generator containing three sockets). Although this separable cluster electrode has demonstrated promising results in a pre-clinical study, until now, the clinical feasibility and effectiveness of this novel device has yet to be demonstrated in human studies.

1. **Objectives**
   1. To evaluate the clinical feasibility and outcomes of switching monopolar RFA using a separable cluster electrode in patients with HCC.
   2. To compare the therapeutic outcomes and safety of the study patients with those of a matched historical control group
2. **Endpoints**
   1. Primary Outcome Measures:
      1. Major complication rate after RFA [ Time Frame: 30 days after RFA ]
      2. Technical success [ Time Frame: 1 day after RFA ]
   2. Secondary Outcome Measures:
      1. Local control (tumor progression) rate [ Time Frame: 12 months after RFA ]
      2. Recurrence-free survival rate [ Time Frame: 24 months after RFA ]
   3. Other Outcome Measures:
      1. Total procedure time [ Time Frame: 1 day after RFA ]
      2. Ablative zone volume [ Time Frame: 1 day after RFA ]
3. **Eligible criteria**
   1. Inclusion Criteria:
      1. HCC diagnosed on biopsy, OR typical imaging features of HCC on CT or MRI according to AASLD guideline
      2. 1-3 HCCs equal to or smaller than 5 cm in the liver
      3. no direct contact with or invasion into the hepatic hilar structures or inferior vena cava
      4. treatment-naïve HCC
      5. Eastern Cooperative Oncology Group performance status of 0
   2. Exclusion Criteria: Patients with any of followings are excluded.
      1. Patients with uncontrolled coagulopathy
      2. Patients with Child-Pugh classification C
      3. Patients with tumor invasion into the portal vein or hepatic vein
      4. Extrahepatic spread
4. **Study design**
   1. Prospective, single-center, single-arm clinical trials
   2. Phase II clinical trials for novel separable cluster electrode which demonstrated potential efficacy and feasibility on pre-clinical study.
5. **Required sample size**
   1. 196 patients with focal liver malignancies
6. **Withdrawal criteria**
   1. All participants have the right to withdraw at any point during the study without risk of future prejudice. Any investigators or medical staffs may discontinue the study procedure(s) in any participant at any time if medically necessary.
   2. If the study procedures are discontinued for any participant, the reason should be recorded, and the primary investigator must be notified promptly. Participants will not be replaced in this study.
7. **General treatment guidelines**
   1. CT Image Acquisition for Image Fusion
      1. Monophasic late arterial phase CT scans on the same day as RFA (Discovery CT750HD; GE Healthcare, Waukesha, WI, USA).
      2. Intravenous administration of a nonionic iodinated contrast agent (1 mL/kg of iopromide, Ultravist 370; Bayer Healthcare, Berlin, Germany) at a rate of 2-4 mL/sec.
   2. RFA
      1. Ablation Protocol
         1. The goal of RFA is to achieve complete ablation of both the index tumor and an ablation margin (0.5 to 1.0 cm) in the normal liver parenchyma.
         2. Conscious sedation, with close monitoring of the vital signs.
         3. Local anesthesia using a subcutaneous injection of 5−15 mL of 1% lidocaine (Dai Han Pharm, Seoul, Korea).
         4. One cycle of ablation for approximately 10 minutes in tumors < 2.5 cm and for 18 minutes in tumors > 2.5 cm.
         5. In cases of incomplete ablation, additional cycle(s) of RFA were done followed by repositioning of the electrode(s), as appropriate.
         6. Active tip adjustment among three options, 2.5 cm, 3.0 cm, and 4.0 cm, depending on the tumor size, location, etc. In general, if the tumor was smaller than 1.5 cm in its longest axis, electrodes with 2.5 cm active tips were used using the “no-tumor-touch” technique [32].
         7. Grounding by attaching four, dispersive pads to the patients’ thighs.
         8. Artificial ascites (5% dextrose solution) for subcapsular tumors or tumors located near the diaphragm
         9. Tract ablation after tumor ablation, by maintaining the active tips at 90 ºC while retracting the electrodes.
      2. Fusion Imaging-guidance
         1. A real time fusion imaging technique between pre-procedural CT imaging and intra-procedural US imaging (PercuNAV; Philips Healthcare, Best, Netherlands).
         2. Conscious sedation of the patients, during image registration for fusion.
         3. (Optional) Artificial ascites instillation before image fusion.
         4. Impedance-switching algorithm to deliver energy
      3. Switching radiofrequency system with a Separable Cluster Electrode
         1. Separable cluster electrode (Octopus®; STARmed), in which the inter-tine distances can be manipulated by the operator.
         2. A 200-watt, multichannel, radiofrequency system (Viva RF System; STARmed) with three independently adjustable generators
         3. Switching monopolar RF energy delivery mode; the active electrode will be switched when the impedance raises 50 Ω above the baseline or when the ablation time passes 30-second.
         4. Circulating chilled normal saline in the lumen of the electrodes.
         5. Other detailed ablation algorithm of energy application according to the manufacturer’s instructions.
   3. Post-RFA imaging
      1. Two phase (arterial, portal) CT imaging with multiplanar reconstruction (axial, coronal, and sagittal) after the RFA.
      2. Intravenous administration of contrast medium (1.35 mL/kg of Ultravist 370; Bayer Healthcare) at a rate of 2.0 to 4.0 mL/s using a power injector.
8. **Follow-up**
   1. initial follow-up one month after the procedure with quadriphasic (unenhanced, arterial, portal, and delayed phase) CT imaging
   2. Subsequent follow-up every three months with quadriphasic (unenhanced, arterial, portal, and delayed phase) CT imaging
9. **Estimates**
   1. All images were analyzed by a blinded radiologist.
   2. Technique success: complete coverage of an index tumor and an extended ablation zone beyond the tumor border on immediate post-RFA CT, according to the standardized terminology of the International Working Group on Image-Guided Tumor Ablation.
   3. Ablation volume = (π × Dmax ×Dmin ×Dvert) / 6

, where Dmax and Dmin are the longest and shortest diameters of the ablation zone (axial image), and Dvert is the longest vertical diameter (coronal) image.

- 1. Total procedure time: the time between the start of planning ultrasonography until the awakening of the patient from conscious sedation
  2. Ablation time: the time when energy was actively delivered via the electrodes
  3. Major complication: events increasing the level of care or lengthening the hospital stay.
  4. Procedure-related death: death within 30 days after the RFA
  5. Post-ablation syndrome: transient and self-limiting symptoms of low-grade fever and/or general malaise.
  6. Technique efficacy: complete ablation of the index tumor on 1 month follow-up CT images
  7. Local tumor progression: tumor foci appeared at the edge of the ablation zone.
  8. Recurrence-free survival: time after RFA during death or the first recurrence of the HCC on follow-up imaging

1. **Post-hoc subgroup analyses**
   1. Purpose: to obtain sufficient statistical power (longer follow-up period) and objectively compare the outcomes of separable cluster electrode with that of routine practice with similar manners.
   2. Endpoints
      1. Primary endpoint: cumulative 1-year, 2-year, and 3-year local tumor progression rates
      2. Secondary endpoint: cumulative 1-year, 2-year, and 3-year recurrence-free survival rates
      3. Tertiary endpoints: technique success rate and major complication rate
   3. End of patients follow-up: July 2015 (2-year after the last patient’s enrollment)
   4. Subgroup: patients with Treatment-naïve HCC (79 patients with 98 HCCs)
   5. Matched historical comparison group (74 patients with 88 HCCs).
      1. From January 2011 to July 2013
      2. Patient who satisfied the same inclusion/exclusion criteria
      3. The same RFA protocols and devices but with multiple internally-cooled electrodes, instead of separable cluster electrodes
2. **Statistical analyses**
   1. Descriptive statistics: technique success rate, ablation volume, total procedure time, ablation time major complication rate, technique efficacy
   2. Survival analyses: time to local tumor progression, recurrence-free survival
      1. Kaplan-Meier curve and log-rank test
      2. Univariate and multivariate Cox proportional hazard regression for potential factors affecting the survival estimates.

1. **Ethical considerations**
   1. Early stopping rule
      1. Major complications are classified according to Common Terminology Criteria for Adverse Event (CTCAE) version 4.0.
      2. If two or more unexpected adverse events with a severity of CTCAE Grade 4 (life-threatening) or 5 (death) are reported, then the Institutional Review Board (IRB) will urgently investigate whether the events are attributable to the study procedures
      3. Depending on the urgent investigation, the IRB can recommend early termination of this study
   2. Potential conflict of interest
      1. Financial support and the investigational RF ablation device for our study were provided by STARmed (Goyang, Korea): grant ID #1441
      2. The authors had complete control of the data and information submitted for publication, which was unbiased by industry.
   3. Ethics and responsibility
      1. This study will be conducted in accordance with the IRB-approved study protocol, the institutional standard operating procedures, the institutional IRB regulations, the International Conference on Harmonisation (ICH) Good Clinical Practice (GCP) guidelines, the Declaration of Helsinki, and applicable government regulations.
      2. The study protocol, Informed Consent Form, and any amendments of them will be submitted to the institutional IRB for formal approval of the study conduct.
   4. Informed consent form
      1. All participants will be given an IRB-approved Informed Consent Form providing sufficient information for participants to make informed decisions about their participation in this study.

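### Local tumor progression, the primary endpoint of the device comparison, is defined per ablation zone, but the named methods assume independent units and no per-patient rule is set; analysed per tumour, the comparison would be mildly anticonservative.

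*Protocol*

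**What the plan says.** - **Tumours per patient.** Eligible criteria (section 5 in the contents list) admits patients with "1-3 HCCs equal to or smaller than 5 cm in the liver".
- **Event definition.** Estimates (section 11) defines local tumor progression as "tumor foci appeared at the edge of the ablation zone". A patient with several treated tumours can have several such zones. By contrast, the same section defines recurrence-free survival by death or the first recurrence, which is a first-event rule for the patient.
- **Role of the endpoint.** Post-hoc subgroup analyses (section 12) makes the cumulative local tumor progression rates at one, two and three years the primary endpoint of the comparison with historical controls.
- **Group sizes.** The same section counts each group both ways: "patients with Treatment-naïve HCC (79 patients with 98 HCCs") and "Matched historical comparison group (74 patients with 88 HCCs").
- **Methods.** Statistical analyses (section 13) lists time to local tumor progression and recurrence-free survival together, with "Kaplan-Meier curve and log-rank test" and univariate and multivariate Cox regression. It states neither the unit of analysis nor a robust variance or frailty term. Technique success appears only among the descriptive statistics.

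**The concern.** The standard log-rank test, the Cox model with model-based variance and the usual Kaplan-Meier intervals all assume that the analysed units are independent. Tumours in one patient share that patient's liver and follow-up, so their times to progression may well be correlated. Device group is constant within a patient. Positive correlation therefore makes the naive standard error of the device contrast too small and its p-value too small on average.

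At stake are the p-value and intervals for the primary endpoint of the only comparative analysis in the Protocol. There is also a choice left open. With no unit stated, a per-tumour and a per-patient result could both be produced and one preferred afterwards. That matters more here because the analysis is labelled post hoc and the group counts are already in the text.

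**Working it through.** The Protocol gives no figure for this point to reproduce. The check asks how far a tumour-level analysis would be off.

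**Inputs from the Protocol:** 79 patients and 98 tumours; 74 patients and 88 tumours; at most three tumours each.

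**Assumptions not in the Protocol:** the within-patient correlation ρ, a nominal two-sided 5% level, and, for the simulation, the event rate and censoring.

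**Step 1: tumours per patient.** 98/79 = 1.24 and 88/74 = 1.19.

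**Step 2: size-weighted mean cluster size,** m = Σm²/Σm. The split into patients with two and three tumours is not given, so both extremes are taken.

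- Study group, 98 − 79 = 19 extra tumours. All pairs: 60 patients with one and 19 with two, (60 + 76)/98 = 136/98 = 1.39. Mostly triples: 69 with one, 1 with two and 9 with three, (69 + 4 + 81)/98 = 154/98 = 1.57.
- Control group, 88 − 74 = 14 extra tumours. All pairs: 60 with one and 14 with two, (60 + 56)/88 = 116/88 = 1.32. Triples: 67 with one and 7 with three, (67 + 63)/88 = 130/88 = 1.48.

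**Step 3: design effect,** DE = 1 + (m − 1)ρ. The correct standard error is √DE times the naive one. The actual level of a nominal 5% test is 2[1 − Φ(1.96/√DE)]. Ranges run over the four values of m.

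| Assumed ρ | DE | Correct SE / naive SE | Actual level |
|---|---|---|---|
| 0.1 | 1.03–1.06 | 1.016–1.028 | 5.4–5.7% |
| 0.3 | 1.10–1.17 | 1.047–1.082 | 6.1–7.0% |
| 0.5 | 1.16–1.29 | 1.077–1.134 | 6.9–8.4% |
| 1.0 (limit) | 1.32–1.57 | 1.148–1.254 | 8.8–11.8% |

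The top of each range applies the study group's most clustered split to both groups. At ρ = 0.5, averaging the two groups' own extremes, (1.57 + 1.48)/2 = 1.52, gives DE = 1.26 and a level of about 8.1%.

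**Step 4: the log-rank test itself.** The design-effect formula was built for means and proportions, so the naive tumour-level log-rank test was also simulated with no device effect. There were 10,000 runs per setting, with a gamma frailty shared within patient, a hazard giving 15% progression at three years when there is no frailty, and censoring uniform between two and four years. Simulation error is about √(0.05 × 0.95/10,000) = 0.2 percentage points.

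| Frailty variance | All multiples are pairs | Mostly triples |
|---|---|---|
| 0 | 4.9% | 5.0% |
| 0.5 | 5.2% | 5.0% |
| 1 | 5.3% | 5.5% |
| 2 | 6.0% | 6.1% |
| 4 | 6.1% | 7.4% |

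The direction agrees with Step 3. The size is smaller, and at frailty variance 0.5 no excess can be seen.

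**The case against.** The strongest objection is that the Protocol never says tumours are the unit. An event defined at a lesion is compatible with a time to the first such event in each patient. The endpoint shares its method line with recurrence-free survival, which is necessarily per patient, and the subgroup is introduced as patients with tumour counts in brackets. On that reading the test compares 79 with 74 patients and nothing is wrong with it. This stands. A reader might infer that the planned p-value is necessarily too small, but the text supports that only conditionally.

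It can also be said that unit and variance method are commonly left to an SAP, which is not at hand and may settle both. That is fair as far as it goes. But the Protocol has its own statistical section that names the tests, and its only definition of the event is per lesion. It sets a first-event rule for one time-to-event outcome and none for the other. That mismatch is in the text shown.

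Three further inferences are not supported:

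- **Technique success.** It is defined as "complete coverage of an index tumor and an extended ablation zone beyond the tumor border on immediate post-RFA CT", so it too is per tumour. A reader might conclude that its confidence intervals are too narrow. The Protocol lists it as descriptive and plans no interval or test for it.
- **All Cox results.** A reader might take every Cox standard error to be too small. That holds for factors fixed within a patient, such as device. For factors that vary between a patient's tumours, such as size, the error can go either way.
- **Recurrence-free survival.** It is a patient-level outcome and is unaffected.

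Finally, the correlation is assumed, and the comparison is post hoc against historical controls. Both limit the weight of the point but do not remove it.

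**Conclusion.** The point holds in conditional form. The Protocol pairs a lesion-level event with methods for independent units and fixes neither a per-patient rule nor an allowance for clustering. If tumours are analysed, the device comparison is mildly anticonservative: correct standard errors are about 2 to 13% larger for an assumed correlation of 0.1 to 0.5. The actual level is about 5.4 to 8.4% by the design-effect formula, or about 5.3 to 7.4% in the simulated log-rank test at frailty variance 1 to 4. The effect is limited because at most 19 of 79 and 14 of 74 patients can have more than one tumour. These figures rest on the assumed correlation or frailty, the assumed 5% level and the simulation's event and censoring rates, none of which the Protocol gives. If patients are analysed, the bias is absent and only the missing statement of the unit remains.

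**What to change.** In Statistical analyses, state that the main analysis of local tumor progression is the time to first local progression in any treated tumour, per patient (79 v 74), using the Kaplan-Meier, log-rank and Cox methods already named. If a tumour-level analysis is kept, use a Cox model with patient-clustered (sandwich) variance in place of the plain log-rank test and the unadjusted Cox model, and label it as secondary. If a tumour-level confidence interval for technique success is ever reported, it should be patient-clustered too. If the SAP already fixes the unit, a cross-reference is enough.

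The cost is a sentence or two and a software option. Tumour-level intervals widen slightly. The per-patient analysis uses fewer units, and its cumulative rates answer a different question from per-tumour rates, because a patient with more tumours has more chances of an event. The tumour counts per patient should therefore be reported for each group alongside it.
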